## Abstract

**Background:**

Daily fiber intake can increase the diversity of the human gut microbiota as well as the abundance of beneficial microbes and their metabolites. Whole-grain wheat is high in fiber.

**Objective:**

This manuscript presents a study protocol designed to understand the effects of different types of wheat on gastrointestinal tract microbes.

**Methods:**

Human adults will consume crackers made from three types of wheat flour (refined soft white wheat, whole-grain soft white wheat, and whole-grain soft red wheat). In this study, participants will alternate between crackers made from refined soft white wheat flour to those made from whole-grain soft white wheat and whole-grain soft red wheat flour. Survey and stool sample collection will occur after 7-day treatment periods. We will assess how wheat consumption affects gastrointestinal bacteria by sequencing the V4 region of 16S rRNA gene amplicons and the inflammatory state of participants’ intestines using enzyme-linked immunosorbent assays. The butyrate production capacity of the gut microbiota will be determined by targeted quantitative real-time polymerase chain reaction.

**Results:**

We will report the treatment effects on alpha and beta diversity of the microbiota and taxa-specific differences. Microbiota results will be analyzed using the vegan package in R. Butyrate production capacity and biomarkers of intestinal inflammation will be analyzed using parametric statistical methods such as analysis of variance or linear regression. We expect whole wheat intake to increase butyrate production capacity, bacterial alpha diversity, and abundance of bacterial taxa responsive to phenolic compounds. Soft red wheat is also expected to decrease the concentration of inflammatory biomarkers in the stool of participants.

**Conclusions:**

This protocol describes the methods to be used in a study on the impact of wheat types on the human gastrointestinal microbiota and biomarkers of intestinal inflammation. The analysis of intestinal responses to the consumption of two types of whole wheat will expand our understanding of how specific foods affect health-associated outcomes.

**International Registered Report Identifier (IRRID):**

DERR1-10.2196/29046

## Introduction

### Background

An individual’s gut microbial community is colonized by trillions of microorganisms [1]. These microorganisms interact with other cells, influencing important metabolic and immune functions. In this way, the gut microbiota can benefit the host, offering protection from pathogens and supporting immune regulation [2]. However, a dysbiotic gut microbiota is linked to disturbances in metabolic and biological processes, leading to a variety of chronic diseases as well as cancers [3]. Individuals with reduced bacterial richness are characterized by phenotypes such as increased adiposity and insulin resistance [3].

Dietary intake is strongly associated with the composition of the gut microbiota [4-9]. This effect of diet on the gut bacterial community can occur within days, quickly switching among functional profiles characteristic of different diets, and thereby making food intake an important factor for managing the gut microbiota [5,10]. The Western diet is characterized by foods low in fiber and high in fat and refined sugars and carbohydrates [11]. The Western dietary pattern results in a gut microbiota characterized by decreased bacterial diversity with specific losses of important microbes such as *Bifidobacterium* spp., *Lactobacillus* spp., and Bacteroidetes [12-15].

As ultraprocessed foods have become a common component of the Western diet, resulting in a loss of whole grains and fiber, the gut microbial composition has become enriched with proinflammatory microbes that correlate with metabolic risk factors and which contribute to noncommunicable chronic diseases such as obesity and type 2 diabetes [14,16,17]. Consumption of whole grains, especially when used as a replacement for refined grains, improves the gut microbiota and is inversely associated with diseases characterized by a gastrointestinal microbial community in dysbiosis [18]. Whole grains have a prebiotic effect on the gut and restore diversity [12]. Prebiotics are compounds known to support the growth of beneficial intestinal microbes [19]. Bifidobacteria and lactobacilli respond positively to increased consumption of whole grains, as observed in a diet intervention study by Costabile et al [12]. Therefore, whole grain consumption may counteract the inhibitory effects of the modern Western diet on these bacterial genera [12,20] and, thus, may be one method to restore gastrointestinal microbiota diversity.

Grains are a staple of the Western diet; however, grains exist in many forms. Thus, it is important to consider the types of grains being consumed [21,22]. The 2015 and 2020 United States Department of Agriculture dietary guidelines for Americans recommended that half of all grains come from whole grains; nevertheless, refined grains are a trademark of the typical Western diet [14,23]. Compared with the consumption of whole grains, consumption of refined grains is associated with a higher risk of chronic disease. In rodent models where the animals are inoculated with human microbiota, low dietary intake of microbiota-accessible carbohydrates for several generations caused reduced microbial diversity [7].

Similarly, in humans, differences in the gut microbiota have been observed among different geographic groups consuming their culturally habitual diets [7,24]. Thus, over subsequent generations, refined grain intake can compound lost intestinal diversity and obliterate some taxa, most specifically Bacteroidales and Clostridiales [7]. Furthermore, the addition of microbiota-accessible carbohydrates to the murine diet suppressed a clinically important intestinal pathogen, *Clostridium difficile* [25]. Recent research has focused on replacing processed foods with whole foods to prevent this loss in microbial diversity and support gastrointestinal health [12,13].

Whole grains are rich in carbohydrates accessible to the gut microbiota, which bacteria can use for food and energy [26]. Consequently, adding whole grains to the diet leads to increased gut fermentation [15]. This process produces short-chain fatty acids, notably butyrate, an important anti-inflammatory and antioxidant molecule [15]. Diets rich in fiber have been positively associated with the presence of bifidobacteria and other lactic acid–producing bacteria and are associated with a shift toward long-term maintenance of metabolic and immune health [15]. Whole-grain wheat is a good source of fiber. Thus, increasing whole-grain wheat intake increases fiber intake, leading to a more diverse microbiome that not only contains the beneficial microbes themselves but also contains their metabolites [27].

Additional components of whole-grain wheat that convey health benefits are polyphenols [28]. Polyphenols act as antioxidants and prebiotics in the gut and, as such, interact with the gut microbial community affecting its composition [29]. When compared with the consumption of refined wheat, consumption of whole wheat increases the absorption of phytochemicals and the subsequent excretion of fecal ferulic acid, a polyphenol metabolite [13,30]. An increase in the availability of fecal ferulic acid through the feeding of whole grains has been associated with a significant increase in *Bacteroidetes* in the gut [13,20]. Thus, the positive relationship between whole grain ferulic acid and certain taxa of the gut microbiota is proposed as a possible mechanism for the alleviation of gut inflammation [13]. As different types of wheat have different polyphenolic content, it is important to understand how they differ in their relationship with the gut microbiota.

### Objectives

To fully understand the impact of whole-wheat products on humans, we must understand the effects of different types of wheat (ie, white vs red or hard vs soft) on human gastrointestinal tract microbes. However, previous studies have ignored these differences in wheat types. Therefore, we describe a protocol in which we will feed human adults crackers made from three different types of wheat flours and assess how cracker consumption affects (1) the gastrointestinal microbial communities and (2) the inflammatory state of the intestines. We hypothesize that whole-grain soft white wheat flour will promote different microbes compared with whole-grain soft red wheat flour. In addition, we expect that the whole-grain soft red wheat treatment will result in decreased intestinal inflammation compared with the refined white wheat flour treatment. The successful completion of the proposed research will improve our understanding of the unique effects of different types of wheat on the human gut microbiota and the inflammatory state of the gastrointestinal tract.

## Methods

### Design

This wheat intervention study will characterize the variable response of gut bacteria to supplementation in adult humans. Treatments will include (1) refined soft white wheat flour, (2) bran-containing whole-wheat flour of Michigan soft white wheat, or (3) bran-containing whole-wheat flour of Michigan soft red wheat. All 3 flour samples will be provided by King Milling Company (Lowell, Michigan). Each of the two whole-wheat interventions will be administered over a 1-week period, with a baseline week (refined soft white wheat flour) before the intervention begins and a washout week (refined soft white wheat flour) between the two test periods (Figure 1). Wheat flour will be administered to participants in the form of wheat crackers. The nutrient composition of the wheat crackers is provided (Table 1)**.** During each of the two test periods, 80 g of crackers made from whole-grain soft white wheat flour or whole-grain soft red wheat flour will provide each participant with approximately 10.7 g of total dietary fiber per day (Table 1). At the end of each 1-week treatment period, a stool sample as well as answers to a health and fiber intake questionnaire, will be collected from each participant. A total of 4 stool samples will be collected from each participant over the course of the study. Microbiome samples will be aliquoted and stored at −80°C until analysis.

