### Outcomes

#### Overview

At the conclusion of each week, stool samples will be collected for analysis. The primary outcome measure will be the alpha diversity of the gut microbiota. This will be measured using the sequencing data obtained from the participants’ stool samples after DNA extraction and polymerase chain reaction (PCR) amplification of the V4 region of the 16S rRNA gene. The secondary outcome measure will be biomarkers of gastrointestinal inflammation, as measured by protein concentrations of calprotectin and lipocalin-2 in protein extracts of the stool samples. Furthermore, the microbiota beta diversity, abundance of *Bifidobacterium* and *Lactobacillus,* and butyrate production capacity of the gut microbiota will be assessed after each week of treatment. The abundance of *Bifidobacterium* and *Lactobacillus* will be determined from the sequencing results. The butyrate production capacity will be determined by quantitative real-time PCR assays targeting the bacterial butyrate kinase and butyrate transferase genes [32].

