### Statistical Analyses

Statistical analysis of differences between pre- and posttests will be assessed using ANOVA or Friedman Wilcoxon rank-sum tests [39]. Multivariate statistics will be performed using R (R Foundation for Statistical Computing), a free statistical software program. To compare the alpha diversity of the microbial communities, Chao1 (a measure of richness), inverse Simpson (a measure of richness and evenness, with emphasis on evenness), and Shannon diversity (a measure of richness and evenness, with emphasis on richness) will be calculated in R using the vegan package [40]. ANOVA and Wilcoxon signed-rank test or Friedman test with post hoc comparisons will be used to compare alpha diversity across treatment categories after intervention [41]. For beta diversity, Bray-Curtis and Sorenson distances will be used with principal coordinates analysis ordination to produce plots of the distances between samples. Differences in beta diversity between time points will be determined using permutational multivariate ANOVA (PERMANOVA) via the adonis function in the vegan package, and differences in group dispersion will be determined using PERMDISP [40]. PERMANOVA may also be used to determine the relationship between the distance metrics and wheat variety, as well as other variables. Metastats (a function of the mothur software package) will be performed on the subsampled abundance data to test for significant differences in operational taxonomic unit abundance between groups [42]. Changes in taxa (both genus and phylum level) >1% average relative abundance will be determined across time points using the Friedman test with post hoc comparisons. Where appropriate, the negative binomial and zero-inflated mixed models in the R package will be used to test for differences in taxa abundance over time [43].

Enterotypes will be manually assigned based on clustering within quadrants in a Bray-Curtis principal coordinates analysis plot overlaid with the most abundant taxa driving community differences, as in Wu et al [4], using the envfit function in the vegan package. Significant differences between enterotypes will be determined using ANOVA for parametric data and the Kruskal-Wallis test for nonparametric data. Differences between time points within each enterotype will be determined using the Friedman test with post hoc comparisons.

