### Response Analysis

If only a subset of participants is found to respond to the treatment, response groups will be determined by an individual’s change in alpha diversity metrics across the treatments. A participant will be considered a *positive responder* if alpha diversity (either Chao1, Shannon, or inverse Simpson) is greater at time points B and D (whole wheat) than at both A and C (refined white wheat). However, if this change is not observed, participants will be considered *nonresponders*. After post hoc assignment of response groups, differences in overall alpha diversity between positive responder and nonresponder groups will be tested with ANOVA (if parametric) or Wilcoxon ranked-sum (if nonparametric). The normality of data will be determined using the Shapiro-Wilk test. Differences will be tested within each time point. Beta diversity differences between response groups will be determined at each time point using PERMANOVA and PERMDISP. Continuous demographic variables (age, BMI, and fiber intake) will be compared with a two-tailed *t* test if parametric and a Wilcoxon rank-sum test if nonparametric, with normality confirmed using the Shapiro-Wilk test. The Fisher exact test will be used to determine the independence of sex, smoking exposure, and race regarding response to treatment. Differences in genera present at >1% average relative abundance will be tested between response groups using a negative binomial model in the MASS package [44].

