## Discussion

### Impact

The primary aim of this study is to measure the alpha diversity of gut microbiota following each week of cracker treatment to determine whether whole-wheat consumption increases alpha diversity. Additional aims are to measure the levels of gastrointestinal inflammation as well as *Bifidobacterium*, *Lactobacillus,* and butyrate-producing bacteria that are present following each treatment. These analyses will elucidate how different types of wheat may affect the gastrointestinal tract microbiota.

Only recently have we begun to understand the mechanism by which whole grains promote health [12,16,21,45]. Various microbes and metabolites have been hypothesized to decrease inflammation; however, much is still unknown [14]. Our aim—to measure how microbial diversity and levels of certain bacteria are affected by whole-wheat intake—will elucidate the potential mechanisms by which whole grains affect health. In addition, little is known about the effects of different types of wheat (eg, white vs red) on the gut microbiota. Specific wheat types have different molecular compositions and may therefore promote different microbes [46-49]. Taking into account the effects of different types of whole wheat will allow us to understand better the food characteristics that underlie the impact of whole-wheat consumption on humans.

We anticipate that the results of this intervention study will have implications for both wheat producers and consumers. Recent trends suggest an increase in the number of consumers who avoid wheat products as part of new diets that emphasize carbohydrate reduction, despite the unclear benefits of avoidance in those without celiac disease [50]. In fact, the risks of avoiding gluten, and subsequently whole grains, include deficiency of micronutrients, fiber, and an increased consumption of refined products, which may outweigh the perceived benefits of avoiding wheat [50]. Understanding how microbes and gastrointestinal inflammation are affected by the consumption of whole-grain wheat may increase the consumption of whole-grain wheat by health-conscious consumers.

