### Strengths and Weaknesses

An important strength of this study is the composition of the crackers. The aim of the study is to test the effect of specific types of wheat; thus, it is important to note that we have created a cracker formulation that is composed almost entirely of the wheat of interest with few additional ingredients. The simple recipe we have developed for the crackers will improve confidence that the differences observed in the microbial community and inflammatory biomarkers are owing to the consumption of the wheat in the study crackers rather than a different ingredient in the treatment food. The quick turnaround from the cracker intake to sample collection also helps strengthen the study. Stool samples will be collected on the final day of each week's cracker intake, ensuring that little time has elapsed between the last cracker intake and stool sample collection. This is important for microbiota analyses as the temporal intake of food is tightly associated with microbial composition [51]. In addition, we will allow sufficient time to pass between each intervention through the use of a washout period. Johnson et al [33] described a minimum 3- to 5-day period between crossing-over diets to allow the microbiome to return to baseline. The crossover design of this study will allow us to perform within-person comparisons, placing less emphasis on interindividual differences in the gut microbiome [33].

A potential limitation of our study may be participant retention. Participants will be expected to consume approximately 80 g of crackers every day for 4 weeks, so it is important that they enjoy the taste of the crackers to ensure their compliance and continuance in the study. However, the study participants may tire of the taste of the crackers. A high dropout rate could hinder our ability to detect statistically significant differences.

Whole grains alleviate dysbiosis in the gut microbiota; however, little is known about the impact of different wheat types on this phenomenon [12,18,20]. A 4-week wheat intervention to investigate the effect of different types of Michigan-grown wheat on the gut microbiota is described in this protocol. The results of this study will improve our understanding of the unique effects of different types of wheat on gut microbiota and on the inflammatory state of the human gastrointestinal tract.

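### Refined crackers always come in weeks 1 and 3 and whole wheat in weeks 2 and 4, so the pooled primary comparison absorbs one week of any linear drift, and no stated alpha-diversity test separates week from treatment

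*Protocol article*

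**What the plan says.** The Design section of the protocol article starts all participants on refined flour, "with a baseline week (refined soft white wheat flour) before the intervention begins", and places "a washout week (refined soft white wheat flour) between the two test periods". It also states: "A total of 4 stool samples will be collected from each participant over the course of the study". The Response Analysis section confirms which sample is which: a positive responder is someone whose alpha diversity "is greater at time points B and D (whole wheat) than at both A and C (refined white wheat". No sequence begins with whole wheat, and no group stays on refined flour throughout.

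The Overview under Outcomes states: "The primary outcome measure will be the alpha diversity of the gut microbiota". The Impact section gives the aim as "to determine whether whole-wheat consumption increases alpha diversity". Under Statistical Analyses, ANOVA with the Wilcoxon signed-rank or Friedman test, followed by post hoc comparisons, is to "compare alpha diversity across treatment categories after intervention". Other analyses in that section work by time point or over time, but there the time point stands in for treatment and is not a term beside it. Strengths and Weaknesses calls the design a crossover and counts the washout as a strength.

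**The concern.** White and red flour may or may not be crossed over; the text does not say and Figure 1 is not shown. Refined against whole wheat, which is the primary question, is not crossed over. Whole-wheat samples are on average taken later than refined ones, in the same way for everyone. Any steady change over the four weeks therefore enters the whole-wheat estimate and can create an effect or hide one.

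The protocol itself describes circumstances in which such a change could arise. A new daily 80 g food displaces cereals and bread from week 1, antibiotics are excluded only for the two weeks before entry, and "the study participants may tire of the taste of the crackers". A washout lets the effect of the previous flour fade. It does nothing about a trend that runs through the whole study.

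**Working it through.** **Inputs.** Weeks A, B, C, D = 1, 2, 3, 4, with refined at A and C and whole wheat at B and D (Design; Response Analysis). n = 30 (Setting and Participant Recruitment). The document states no alpha, power, SD or drift, so there is no figure of its own to reproduce. Assumed here: two-sided 0.05, independent weekly errors with equal variance σ², and linear drift of d within-person SDs per week.

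**Drift in each contrast** (sum of coefficient × week):

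| Contrast | Weeks of drift | Variance (σ²) |
|---|---|---|
| (B+D)/2 − (A+C)/2 | 3 − 2 = +1 | 1.0 |
| B − A | +1 | 2.0 |
| D − C | +1 | 2.0 |
| B − C | −1 | 2.0 |
| D − A | +3 | 2.0 |
| B − (A+C)/2 | 2 − 2 = 0 | 1.5 |
| D − (A+C)/2 | 4 − 2 = +2 | 1.5 |

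**False positives for the pooled contrast, no true effect.** The contrast has variance σ² per participant, so the noncentrality is d × √30. Paired t test, 29 df:

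- d = 0.1: 8.3%
- d = 0.2: 18.5%
- d = 0.3: 35.6%
- d = 0.4: 56.3%

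With a pooled repeated-measures error on (30 − 1) × (4 − 1) = 87 df, the last three become 19.2%, 36.9% and 58.2%.

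**With a linear week term.** Regressing on whole wheat (0, 1, 0, 1) and week (1, 2, 3, 4), the whole-wheat estimate is (−A + 3B − 3C + D)/4.

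- Drift: (−1 + 6 − 9 + 4)/4 = 0.
- Variance: (1 + 9 + 9 + 1)/16 = 1.25σ², against 1.00σ² unadjusted. √1.25 = 1.118, so the SE is 12% larger.
- Simulated type I error (20,000 trials): 0.050 at d = 0.2 and 0.051 at d = 0.5, against 0.186 and 0.756 unadjusted.

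**Separate flour terms plus linear week, if flour order is fixed.** The week-2 flour's estimate stays B − (A+C)/2, variance 1.5σ². The week-4 flour's becomes 0.5A − 1.5C + D, variance 0.25 + 2.25 + 1 = 3.5σ² against 1.5σ². √(3.5/1.5) = 1.53, so the SE is 53% larger.

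**Limits of adjustment.** Categorical weeks together with treatment give 5 columns of rank 4, so they cannot be fitted. For an illustrative drift whose weekly step halves (0, 1, 1.5, 1.75), bias falls from (1 − 1.5 + 1.75)/2 = 0.625 to (3 × 1 − 3 × 1.5 + 1.75)/4 = 0.0625. It is reduced but not gone.

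**The case against.** The strongest reply is that drift may be small. The first sample follows a full week on refined crackers, so the new food and the displaced bread are present at all four samples. The document says that diet acts on the microbiota within days, cites 3 to 5 days for a return to baseline and describes the adult microbiota as stable. Tiring of the crackers is raised as a retention and compliance risk, not as a trend in diversity. A weekly score is to account for fibre from other foods, which covers one route of background change. All of this stands as reason to think drift modest. None of it shows drift to be absent, and no stated analysis would detect or remove it by design.

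Three stronger readings are tempting, and the documents do not support them.

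- A reader might infer that every comparison is shifted by one week. That is exact only for the pooled and adjacent-pair contrasts. Single-flour contrasts run from −1 to +3 weeks, and week 2 against the mean of weeks 1 and 3 carries none.
- A reader might infer that the plan ignores the return to refined flour at C. The responder rule does require B to exceed the later C. In simulation with one index and no effect, its chance responder share moves only from 16.7% with no drift to 20.6% at 0.2 SD per week. Post hoc comparisons across four time points could also show C against A. Neither is planned as a drift check or adjusts the primary comparison.
- A reader might infer that one extra term cures the problem for 12% more SE. That holds only for linear drift and pooled flours, and the stated plan has no mixed model for alpha diversity to which the term could simply be added.

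An unseen analysis plan might add a week covariate. The point rests on the tests that the article does name for its primary outcome.

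**Conclusion.** The point holds for the pooled whole-wheat versus refined comparison of alpha diversity. The fixed alternation shifts it by exactly one week of any linear drift, and the named tests treat weeks only as treatment labels. The false-positive rates, about 8% to 56% for drifts of 0.1 to 0.4 SD per week, show sensitivity. They are not an estimate of what will happen, because the document gives neither a drift nor a within-person SD. It does not follow that drift is present or that a positive result would be spurious. Because the bias would fall on the primary outcome and the analysis can still guard against the linear part, the change should be made. Making the linearity-dependent estimate the only primary result is debatable, so both estimates belong in the report.

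**What to change.** For the pooled comparison, fit alpha diversity on whole wheat (0/1), linear week (1 to 4) and a participant random intercept. Report the week-adjusted and unadjusted estimates side by side, and claim a whole-wheat effect only if it survives the adjustment. If a rank test is preferred, apply the signed-rank test to each participant's (−A + 3B − 3C + D)/4. Report C − A as a planned check on drift and carry-over. Keep separate flour terms for the white versus red question.

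The Results section says that samples were collected in summer 2019, so the order cannot change, but the analysis needs no new data. The cost is about 12% more SE for the pooled contrast, and up to about 53% more for the week-4 flour if flour order is fixed and each flour has its own term. State two limits: non-linear drift is only partly removed, and categorical week effects cannot be estimated beside treatment.
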